**5.1.2 Frozen Plasma**

Patients randomized to FP will receive 3 U for IBW≤60 kg or 4 U for IBW>60 kg (corresponding to weight-base dosing range of 10–15 mL/kgIBW rounded up to 1 U increment, up to a maximum of 4 U per dose) for each order during the first 24 hours after randomization. FP will be provided by the Canadian Blood Services and will be stored, thawed, and pooled by the blood bank according to current standards. FP will be infused as per standard hospital protocols at the participating institutions (i.e., infused using timing recommended in the current monograph through standard 140 µm blood infusing set).

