#### **7.2.3 Bleeding Data**

The comparison of 'major' bleeding based on the validated e-CABG and universal definition of perioperative bleeding (UDPB) in cardiac surgery (1, 72) (Table 4) will be assessed. The UDPB is a multistage definition for perioperative bleeding based on easily measured clinical end points, including total blood loss from chest tubes within 12 hours, allogeneic blood products transfused, surgical re-exploration including cardiac tamponade, delayed sternal closure, and the need for salvage treatment.

Depending on these components, bleeding is graded as insignificant, mild, moderate, severe, or massive. (Table 4) (72).

**Table 4 Bleeding categories according to the UDPB in adult cardiac surgery (if different categories indicate mixed definitions of bleeding, the worst definition applies) (72)**

| Bleeding definition     | Postoperative chest tube blood loss within 12 h (mL) | RBC (units) | FP (units) | PLT (units) | Cryoprecipitate | PCCs | rFVIIa | Reexploration /tamponade |
|-------------------------|------------------------------------------------------|-------------|------------|-------------|-----------------|------|--------|--------------------------|
| Class 0 (insignificant) | <600                                                 | 0           | 0          | 0           | No              | No   | No     | No                       |
| Class 1 (mild)          | 601–800                                              | 1           | 0          | 0           | No              | No   | No     | No                       |
| Class 2 (moderate)      | 801–1000                                             | 2–4         | 2–4        | Yes         | Yes             | Yes  | No     | No                       |
| Class 3 (severe)        | 1001–2000                                            | 5–10        | 5–10       | N/A         | N/A             | N/A  | No     | Yes                      |
| Class 4 (massive)       | >2000                                                | >10         | >10        | N/A         | N/A             | N/A  | Yes    | N/A                      |

FP, frozen plasma; N/A, not applicable; PCC, prothrombin complex concentrate; PLT, platelets; rFVIIa, recombinant activated factor VII; UDPB, universal definition of perioperative bleeding.

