#### 4.6 Efficacy

The primary population for the analysis of the efficacy of the IMPs will be the ITT. The primary efficacy endpoints will also be analyzed for the PP population.

The analysis of efficacy will focus on the following primary endpoints:

P1. Treatment response, defined as effective if no additional hemostatic intervention (such as administration of hemostatic agents including a second dose of IMP, platelet transfusion, or surgical re-exploration) in the time windows

- from 60 minutes to 4 and 24 hours after initiation of the first dose of IMP,
- *from initiation of the first dose of IMP to 4 and 24 hours.*

Otherwise, treatment response will be considered as not effective, see section 6.1. If the dose of IMP is repeated within less than 60 minutes, treatment response to the IMP will be assessed for the time frames after the second IMP dose only.

P2. Amount of allogeneic blood products (for each type of product and cumulatively) administered

- during the first 24 hours after the start of surgery,
- *during the first 24 hours after the end of CPB,*
- *during the first 24 hours after randomization,*
- *during the first 24 hours after the start of first IMP dose.*

P3. Number of patients who do not receive any allogeneic blood product (in total and for each type separately)

- during the first 24 hours after the start of surgery,
- *during the first 24 hours after the end of CPB,*
- *during the first 24 hours after randomization,*
- *during the first 24 hours after the start of first IMP dose.*

In addition the following efficacy endpoints will be explored:

S1. Number of partial or full IMP doses of PCC and FP administered

- during the first 24 hours after the start of surgery.
- *during the first 24 hours after the end of CPB,*
- *during the first 24 hours after randomization,*
- *during the first 24 hours after the start of first IMP dose.*

|                           |                 |             |               |
|---------------------------|-----------------|-------------|---------------|
| Statistical Analysis Plan | Version 2.0     |             | Page 13 of 19 |
| Sponsor                   | [name] | Protocol No | FARES         |

S2. Incidence of major bleeding, using the universal definition of perioperative bleeding (UDPB) in cardiac surgery scores and their individual components

- during the first 24 hours after start of surgery,
- *during the first 24 hours after the end of CPB,*

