Otherwise, treatment response will be considered as not effective. If the dose of IMP is repeated within less than 60 minutes, treatment response to the IMP will be assessed as not effective.

Furthermore, the above mentioned efficacy endpoints will be exploratory analyzed in time frames which start at the time of first IMP dosing instead of the start of the surgery (as specified in section 2.2 of this SAP).

The following analysis methods will be applied to the different endpoints in according to their data type:

The analysis of categorical variables (P1, P3, S2, S4, S5, S6) will present relative frequency tables and estimates of the proportions with 95% confidence intervals separately in the treatment groups. The proportions will be compared between the treatment groups by means of Fisher's exact test.

The analysis of continuous variables (S7, S8) will present descriptive statistics of the sampling distribution and the differences between treatment groups. Also 95% confidence intervals and results of t-test of the treatment group differences will be reported.

The analysis of integer count variables (P2, S1, S3) will present descriptive statistics of the sampling distribution and the differences between treatment groups. Treatment group comparisons for variables (P2, S3) will be performed in the context of a counting regression model for the ABPs and their components (SAS PROC GENMOD with Negative-Binomial distribution). Tests and 95% confidence intervals for the treatment group differences will be derived from this statistical model and reported. The analysis for the sum of the allogenic blood products transfused (P2, S3) will be repeated analogously for the adjusted sum of the allogenic blood products transfused (cf. section 6.1), excluding FP.

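### SAP endpoint S2 applies Fisher's exact test equally to the unmodified and modified UDPB, with no class defined as major and no use of the class order; on the unmodified scale every cut-off is either saturated or tilted by the allocated product.

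*Combined protocol and SAP*

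**What the plan says.** The protocol (7.2.3) plans "The comparison of 'major' bleeding based on the validated e-CABG and universal definition of perioperative bleeding (UDPB) in cardiac surgery". It describes UDPB as an ordered scale: "bleeding is graded as insignificant, mild, moderate, severe, or massive". Table 4 scores each component separately, and "if different categories indicate mixed definitions of bleeding, the worst definition applies". The same section then adds a modified UDPB that omits the PCC and FP components, because the randomization schedule dictates their use.

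SAP 4.6 carries this into S2 as "Incidence of major bleeding, using the universal definition of perioperative bleeding (UDPB) in cardiac surgery scores and their individual components", in four time windows, together with the modified version. For the method it states: "The analysis of categorical variables (P1, P3, S2, S4, S5, S6) will present relative frequency tables and estimates of the proportions with 95% confidence intervals", and then: "The proportions will be compared between the treatment groups by means of Fisher's exact test". It makes no distinction between the two versions of the score. SAP 6.1, which derives treatment response and the blood-product sums, has no entry for major bleeding.

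On dose, protocol 5.1.2 states: "Patients randomized to FP will receive 3 U for IBW≤60 kg or 4 U for IBW>60 kg". Protocol 3.2 applies the randomized product to the first and second orders, with FP in both arms from the third.

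**The concern.** An incidence needs a threshold, and none is given. With four possible cut-offs (class 1, 2, 3 or 4 and above), four windows and two score versions, 4 × 4 × 2 = 32 different proportions fit the text. If the class is not fixed in advance, it can be chosen after the results are seen.

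The unmodified score has a second problem: the study products are themselves scoring components. FP units count towards classes 2, 3 and 4, while PCC counts only towards class 2. A significant result on that score could reflect which product was allocated and not how much the patient bled.

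Third, neither a two-by-two Fisher test nor one over all five classes uses the order of the classes.

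This matters because the pilot exists to help choose a Phase 3 endpoint, and UDPB is the only bleeding-severity score in the SAP's S2. The protocol also lists e-CABG, which S2 drops.

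**Working it through.** The documents give no power, effect size or event rate for S2, so there is no planned figure to reproduce. The check has two parts.

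**Part 1. Cut-offs on the unmodified scale (documents only)**

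Inputs:
- Table 4: FP 2–4 U or any PCC = class 2; FP 5–10 U = class 3; FP >10 U = class 4; PCC not applicable in classes 3 and 4; the worst component decides.
- FP dose 3 or 4 U by ideal body weight; two randomized doses at most.
- The SAP ITT population requires at least one treatment with PCC or FP.

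| Study doses received | FP arm | PCC arm |
|---|---|---|
| One full dose | 3 or 4 U = class 2 | PCC given = class 2 |
| Two full doses | 2 × 3 = 6 U or 2 × 4 = 8 U = class 3 | PCC given = class 2 |
| Further FP units to reach class 3 (5 U) after two doses | none | 5 |
| Further FP units to reach class 4 (11 U) after two doses | 11 − 6 = 5, or 11 − 8 = 3 | 11 |

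Thus:
- Class 1 or 2 and above: about 100% in both arms by construction. The exceptions are FP patients given less than 2 U and first doses outside the window.
- Class 3 or 4 and above: reached with fewer additional FP units in the FP arm, because its allocated units already count.

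No cut-off is both informative and neutral.

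**Part 2. Ordinal against dichotomised test on the modified scale (assumptions needed)**

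From the documents: 50 evaluable per arm. Assumed: two-sided 0.05; a common odds ratio (OR) shifting PCC towards lower classes; and six control-arm distributions over classes 0–4 (%): 10/15/40/25/10, 20/20/35/20/5, 20 in each, 5/10/35/35/15, 15/15/50/15/5, 30/25/30/12/3. The row at OR 2.4 borrows the size of the red-cell-avoidance odds ratio in protocol 1.1, which is not a UDPB effect.

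Methods: for each control cumulative proportion s, the PCC odds are [s/(1 − s)]/OR. Fisher power is the exact sum of the two binomial probabilities over tables with p ≤ 0.05. Wilcoxon power is tie-corrected, from 40,000 simulated trials per scenario. Ranges are over the six distributions.

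| OR | Wilcoxon | Fisher, class ≥2 | Fisher, class ≥3 | Power ratio at ≥2 | Power ratio at ≥3 |
|---|---|---|---|---|---|
| 1.5 | 19–21% | 8–13% | 5–13% | 1.5–2.6 | 1.5–3.8 |
| 2.0 | 46–49% | 21–35% | 10–33% | 1.4–2.3 | 1.4–4.5 |
| 2.4 | 65–68% | 34–53% | 15–49% | 1.3–1.9 | 1.4–4.5 |
| 3.0 | 84–86% | 55–72% | 21–67% | 1.2–1.5 | 1.3–4.0 |

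Part of the gap is Fisher's conservatism. With no true difference it rejects in about 2.4–3.5% of trials at these cut-offs, against about 5% for Wilcoxon.

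**When odds are not proportional.** Three scenarios put the effect only at the class 3 boundary:

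| Control | PCC | Wilcoxon | Fisher, class ≥3 |
|---|---|---|---|
| 10/15/40/25/10 | 10/15/55/15/5 | 18% | 32% |
| 10/15/40/25/10 | 10/15/60/10/5 | 28% | 57% |
| 20/20/30/20/10 | 20/20/50/7/3 | 19–20% | 64% |

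Here the ordinal test is the weaker one.

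**The case against.** The case for leaving S2 alone has real force. S2 is exploratory, no endpoint in this pilot is powered, and the SAP calls its methods primarily descriptive, so the power of one exploratory test is a secondary matter. The protocol has already identified the product bias and built the modified score to remove it. The SAP also promises frequency tables and component results.

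Three stronger readings are tempting, and the documents do not support them:

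- *An ordinal test would roughly double power.* That holds for particular assumptions only. With 15/15/40/22/8% and OR 2.0, Wilcoxon has 48% power against 24% for Fisher at class 3 and above. At class 2 and above Fisher has 31%, a ratio of 1.5, and by OR 3.0 that ratio is 85/71 = 1.2. The documents give no distribution, effect size or cut-off that would select one of these figures.
- *The SAP discards the five classes.* It does not say so. A five-class table, and even a Fisher test over all five classes, would fit its wording. That test would still ignore the order.
- *The product bias was overlooked.* It was not. Protocol 7.2.3 names it.

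The objection leaves three gaps standing: major has no definition, the product-driven score receives the same test as the corrected one, and the order is unused. Replacing incidence by an odds ratio alone would also depart from the protocol's endpoint, so the incidence should stay.

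**Conclusion.** The point holds as a minor one. The missing definition of major, and the lack of a neutral and informative cut-off on the unmodified UDPB, follow from the documents alone. They rest only on Table 4, the study doses and the treated ITT population.

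The gain from an ordinal test is conditional. It is about 1.2 to 4.5 times Fisher's power at class 2 or 3 and above, with 50 per arm, the six assumed distributions, proportional odds and OR 1.5 to 3.0. It can become a loss when the effect is confined to one class boundary. The case for change therefore rests mainly on the undefined threshold and the product-driven test.

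**What to change.** In SAP 4.6, before unblinding:

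1. Make the modified UDPB the main version of S2. Show all five classes by arm, and compare arms with a Wilcoxon test and a proportional-odds odds ratio with 95% CI.
2. Keep the protocol's incidence endpoint: state in SAP 6.1 which class or classes of the modified scale count as major, and report that proportion by arm with its 95% CI alongside the ordinal result. This covers the case where the effect sits at one boundary.
3. Report the unmodified UDPB descriptively, without a between-arm test.
4. Record the change in SAP 2.2, which currently declares no deviation from the protocol's statistical methods.

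The cost is a few lines of SAP text and one extra model. No new data are needed. The odds ratio assumes roughly proportional odds, so it should be read next to the class table.

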### **4.4 Assignment of Patients to Treatment Groups**

Patients will be assigned to treatment with either PCC or FP using a permuted-block, stratified (by centre) random allocation scheme prepared by a biostatistician not involved in the conduct of the trial. Group allocation will apply to the first two doses of IMP during the treatment period (up to 24 hours from randomization). For any additional doses (i.e., the third dose and thereafter), patients in both groups will receive FP. Subjects/patients are not permitted to re-enroll in the study.

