### 9.2 Statistical Analysis

For the statistical analysis of the efficacy parameters the following analysis populations will be considered:

The statistical analyses will be performed on the intention to treat (ITT) population, which will include all randomized and treated patients who consent to the study. Randomized patients who did not undergo cardiac surgery or received no IMP will be excluded from the analysis. It is anticipated that <20% of patients will fall into these categories. In the event that a patient receives treatment that is not in concordance with the randomization schedule, the treatment group will be defined according to the randomization (rather than the actual treatment received).

The per-protocol (PP) population: This analysis population will consist of all patients in the ITT population, excluding patients with important protocol deviations that may affect the statistical analysis. The following patients will be excluded by default:

- Patients who receive an IMP different to the IMP assigned by randomization
- Patients who receive less than 80% of the planned dose
- Patients who significantly violate inclusion/exclusion criteria

A final decision about the classification of protocol deviations and their consequences regarding assignment of patients to analysis populations will be made during the data review meeting prior to the final analyses. Decisions and outcome will be approved by the Principal Investigator (Sponsor) in consultation with the funder (Octapharma).

The ITT analysis population is considered the primary population for analysis of the efficacy objectives.

Descriptive statistics with 95% confidence intervals will be used to describe the data. Simple tests of comparison will be used to compare outcomes between the two groups. The summary tables and exploratory inferences will be chosen according to the scaling level of the measurements, e.g. frequency tables and Chi-square tests for categorical responses, sampling statistics and F-tests for continuous data.

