## 9.3 Randomization, Stratification, and Code Release

Eligible patients will be randomly assigned to receive either *Octaplex* or FP. Randomization lists using a permuted-block, randomization scheme (stratified by site) will be prepared by the biostatistician. Sealed randomization envelopes based on the randomization lists will then be provided to the blood banks of the participating centres who will be responsible for providing the IMP.

Patients will be identified using a sequential numbering system within the centre. Randomization will then be performed in sequential order of the patient IDs.

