### 4.1.3 Pooling of centers

No pooling of centers will be performed (only two centers are involved in the study).

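### Randomisation is stratified by centre, but no comparison in SAP 4.6 accounts for it, and the categorical endpoints, including primary endpoints P1 and P3, have no pre-specified between-arm effect with a confidence interval

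*Combined protocol and SAP*

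**What the plan says.** **Allocation.** Protocol 4.4 describes a "permuted-block, stratified (by centre) random allocation scheme", and Protocol 9.3 repeats it: "Randomization lists using a permuted-block, randomization scheme (stratified by site) will be prepared by the biostatistician". Protocol 3.3.5 relies on the same stratification. Centre is the only stratification factor, and there are two centres.

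**Centre in the analysis.** The SAP's only statement on handling centre is in 4.1.3: "No pooling of centers will be performed (only two centers are involved in the study", with nothing after it on stratified or by-centre analysis.

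**Categorical endpoints (P1, P3, S2, S4, S5, S6).** SAP 4.6 asks for relative frequencies and "estimates of the proportions with 95% confidence intervals separately in the treatment groups". It continues: "The proportions will be compared between the treatment groups by means of" Fisher's exact test.

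**Other endpoints.** For S7 and S8, SAP 4.6 presents group differences: "Also 95% confidence intervals and results of t-test of the treatment group differences will be reported". For P2 and S3 a negative-binomial model supplies tests and intervals for the treatment difference. S9, the conservative response definition added in SAP version 2.0, appears in none of the method lists.

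**Protocol wording.** Protocol 9.2 gives, as examples, "frequency tables and Chi-square tests for categorical responses, sampling statistics and F-tests for continuous data".

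**The concern.** Two things do not fit the design.

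First, when allocation is balanced within centre, the analysis should reflect it. If response differs between the two hospitals, an unstratified comparison carries between-centre variation that the design has already removed, and its standard error is too large.

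Second, two of the three primary endpoints get less than mortality or time to leaving the operating room: two separate intervals and a p-value. A Phase 3 trial of non-inferiority or superiority is planned around the difference between arms and the uncertainty in it. Two arm-wise intervals do not show that uncertainty directly, and comparing them by eye for overlap can mislead. The pilot exists to choose the Phase 3 endpoint, and P1 and P3 are candidates, so the gap falls on endpoints that matter.

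**Working it through.** **Inputs.** 120 randomised and at least 100 evaluable, 50 per arm (Protocol 9.1, SAP 1.3). The implied loss is 1 − 100/120 = 16.7%, within the <20% anticipated in Protocol 3.3.8. The documents give no effect size, power or margin, so there is no power figure to reproduce. The event counts, response rates and centre effects below are illustrative assumptions unless a source is named. Tests are taken as two-sided at 5%, which is also assumed.

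**1. Which endpoints have a between-arm estimate with an interval**

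| Endpoint | Between-arm estimate with CI | Centre included |
|---|---|---|
| P1, P3, S2, S4, S5, S6 | none specified | no |
| P2, S3 | yes, negative-binomial model | no |
| S7, S8 | yes, difference with t-test | no |
| S9 | no method stated | no |
| Mortality (SAP 4.7.1) | yes, risk ratio | no |
| SAP 4.8 variables | yes, treatment differences | no |

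**2. The interval that is not reported.** Take 35/50 versus 30/50.

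- As planned: arm-wise 95% CIs (exact) of 55.4–82.1% and 45.2–73.6%, and Fisher p = 0.40.
- Wilson limits: 0.5625 to 0.8090 for 0.70, and 0.4618 to 0.7239 for 0.60.
- Newcombe lower limit: 0.10 − √[(0.70 − 0.5625)² + (0.7239 − 0.60)²] = 0.10 − 0.185 = −0.085.
- Newcombe upper limit: 0.10 + √[(0.8090 − 0.70)² + (0.60 − 0.4618)²] = 0.10 + 0.176 = +0.276.

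The result is +10 points, 95% CI −8.5 to +27.6. Other cases:

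| Counts | Difference (points) | Newcombe 95% CI | Fisher p | Chi-square p |
|---|---|---|---|---|
| 40/50 vs 30/50 | +20 | 2.0 to 36.4 | 0.049 | 0.029 |
| 35/50 vs 25/50 | +20 | 0.8 to 37.2 | 0.066 | 0.041 |
| 16/50 vs 8/50 | +16 | −0.8 to 31.8 | 0.10 | 0.061 |
| 8/50 vs 4/50 | +8 | −5.3 to 21.4 | 0.36 | 0.22 |

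Half-widths run from about 13 to 19 points (18.9 at 25/50 in both arms). In the second row the arm-wise intervals overlap (55.4–82.1% and 35.5–64.5%), the interval for the difference excludes zero, and Fisher does not reject. The test and the interval should therefore be chosen together.

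**3. How conservative Fisher is at 50 per arm (exact enumeration)**

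| True rates | Fisher | Chi-square |
|---|---|---|
| 50% in both arms (size) | 3.5% | 5.7% |
| 70% in both arms (size) | 3.1% | 5.0% |
| 90% in both arms (size) | 1.8% | 5.1% |
| 80% vs 60% (power) | 52% | 60% |
| 32.7% vs 16.8% (power) | 38% | 46% |
| 16% vs 7% (power) | 18% | 30% |

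The last two rows use red-cell avoidance rates derived from two propensity-matched studies in Protocol 1.1: 100 − 67.3 and 100 − 83.2; 100 − 84 and 100 − 93.

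**4. What centre adds (100,000 simulations, 25 per arm per centre assumed)**

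| Scenario | Fisher | Chi-square | Mantel-Haenszel |
|---|---|---|---|
| Strong centre effect: 35% vs 60% and 65% vs 85% (power) | 57% | 66% | 68% |
| No centre effect: 50% vs 72.5% (power) | 57% | 65% | 65% |
| Null, centres at 35% and 65% (size) | 2.8% | 4.6% | 5.0% |
| Null, both centres at 50% (size) | 3.6% | 5.9% | 5.9% |

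Stratifying gains about 2 power points over chi-square with a strong centre effect, and nothing without one. Most of the gap between Fisher and Mantel-Haenszel comes from Fisher itself.

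**5. S7.** With correlation ρ between the pre-dose and post-dose values, and equal variances at the two times, the ANCOVA variance divided by the change-score variance is (1 − ρ²)/[2(1 − ρ)] = (1 + ρ)/2. That is 0.65, 0.75 and 0.85 at ρ = 0.3, 0.5 and 0.7. The ratio does not hold if the two variances differ.

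**6. Phase 3 sizing from arm proportions alone.** With n per arm = [1.96√(2p̄q̄) + 0.8416√(p₁q₁ + p₂q₂)]²/(p₁ − p₂)², rates of 16.8% and 32.7% give (1.196 + 0.505)²/0.159² = 114.5, so 115 at 80% power. Rates of 7% and 16% give 197.

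**The case against.** The strongest reply is that this is a descriptive pilot with no power calculation, so test efficiency is secondary. The point difference follows by subtraction from two reported proportions, and anyone can compute its interval from the counts. Step 6 shows that arm proportions are enough to run a sample-size formula. With two centres the stratification gain is slight. Exact versus asymptotic testing is largely a preference, and chi-square can exceed its nominal size (5.9% in one null case above). All of this stands, and it limits the weight of the point.

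It does not remove the point. The SAP already specifies between-arm intervals for P2, S7, S8 and mortality, so leaving them out for P1 and P3 does not follow from a policy of pure description. An interval chosen in advance is also better than one picked after the data are seen.

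A reader might infer more than the documents support:

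- *That the pilot yields no between-arm estimate.* It yields several; see the first table in the working.
- *That no analysis uses baseline information.* SAP 3.6 plans subgroups by sex, complexity and urgency, with conditional covariate models, and S7 is itself a change from the pre-dose value.
- *That Fisher breaches the protocol, contrary to the statement of no deviations in SAP 2.2.* Protocol 9.2 offers "frequency tables and Chi-square tests for categorical responses" only as an example, and Protocol 9 leaves the details to the SAP.
- *That SAP 4.1.3 forbids combining the centres.* Its parenthesis suggests the usual convention about merging small centres, and nothing else in the SAP implies separate analyses by centre.

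**Conclusion.** The point holds as an inexpensive improvement that should be made. The comparisons in SAP 4.6 do not use the randomisation stratum, and two of the three primary endpoints lack a pre-specified between-arm effect with an interval. The interval is the more useful part: at 50 per arm its half-width is about 13 to 19 points, and those planning Phase 3 should see that uncertainty beside the estimate. The centre part is mainly about matching the analysis to the design.

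Replacing Fisher with chi-square, taken alone, would be a preference. It cost 8 to 12 power points in the cases run, but the pilot makes no claim to power.

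The sizes rest on 50 evaluable patients per arm, two-sided 5% tests, the illustrative counts and rates shown, and, for centre, an even split between hospitals with an assumed centre effect. The documents give no design rates or centre sizes. What the SAP does and does not specify depends on none of these assumptions.

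**What to change.** - **P1, P3, S2, S4–S6 and S9:** report a centre-stratified Mantel-Haenszel risk difference with 95% CI, naming the interval method (for example stratified Newcombe or Miettinen-Nurminen), and the Cochran-Mantel-Haenszel test. Keep the arm-wise proportions. Keep Fisher for sparse tables, for example where an expected count is below 5. Add S9 to the categorical method list.
- **P2 and S3:** add centre to the negative-binomial model.
- **S8:** compare arms in a linear model with treatment and centre.
- **S7:** use ANCOVA on the post-dose value, with the pre-dose value and centre as covariates.
- **SAP 4.1.3:** state that the centres are combined for analysis, with centre as a stratification factor.

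The cost is SAP wording and a few lines of code, with no new data and no change to conduct. The changes belong in the SAP before unblinding; made later, they should be labelled post hoc.
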